## Abstract

**Background:**

Short-term mindsets interfere with the consideration of future consequences and therefore predict negative behaviors. We developed a smartphone-based intervention aiming to increase a future-oriented mindset and personal goal attainment by strengthening future self-identification and stimulating episodic future thinking. The aims of the study are 1) to examine users' experiences with the application and their treatment adherence, 2) to examine the effectiveness of the intervention, and 3) to explore which intervention modules generate the strongest changes in key outcomes.

**Methods:**

First-year university students (*N* = 166) will be randomly assigned to two conditions: 1) the smartphone-based intervention, or 2) a goal-setting control group. The intervention consists of three week-long modules. Data will be collected at the start of the intervention, at weekly intervals during the intervention, immediately after the intervention, and at 3-month follow-up (and at parallel time points for the control group). We will assess users' experiences, application usage data, primary intervention outcomes (e.g., self-defeating behavior, future orientation, future self-identification), and secondary intervention outcomes (e.g., psychosocial wellbeing, self-efficacy).

**Discussion:**

The study will provide information about users' experiences with the application, the intervention's general effectiveness, and which intervention modules show most promise. This information will be used to further develop the application and optimize this novel intervention.

**Trial registration:**

The trial is registered in the Netherlands Trial Register (number: NL9671) on 16 August 2021.

## Introduction

1

Short-sighted behaviors, such as substance use, overspending, and unhealthy diets, are known to be generally self-defeating and to generate adverse consequences across a variety of domains (e.g., health, well-being, finance; Hershfield et al., 2011; Rutchick et al., 2018). Such behaviors tend to offer immediate gains, benefitting the ‘present self’, while instilling costs in the longer run, and hence harming the ‘future self’ (Van Gelder et al., 2013, Van Gelder et al., 2022). Conversely, being oriented towards the future stimulates behaviors beneficial to one's psychosocial development and well-being (e.g., Steinberg et al., 2009). To stimulate a future-oriented mindset and personal goal attainment, we developed the smartphone-based intervention ‘FutureU’. The goal of the current study is to examine users' experiences and the intervention's effects in order to further develop the intervention.

### Theoretical framework of the intervention

1.1

One class of perspectives on intertemporal decision making (i.e., decisions involving tradeoffs between costs and benefits occurring at different timepoints; Frederick et al., 2002) attributes differences in short-sighted versus future-oriented decision making to the discrepancy between the needs and wants of the present self versus those of the future self (Hershfield, 2011, Hershfield, 2018). Short-sighted decisions and behaviors, according to these perspectives, result from a lack of psychological connection with the self in the future. When feeling disconnected from the future self, discounting one's “own” future utility may be no more irrational than discounting the utility of someone else (Frederick et al., 2002). Conversely, a strong sense of psychological connection between the present and the future self is likely to result in decision making favoring the future self by prioritizing the future over the present (Hershfield, 2018).

Previous research has shown that strengthening identification with the future self can stimulate a future-oriented mindset and affect behavior in a variety of domains, including health (Rutchick et al., 2018), delinquency (Van Gelder et al., 2015, Van Gelder et al., 2022), and saving (Hershfield et al., 2011). Most research investigating future self-identification has focused on the effects of exposure (imaginal or through images) to the future self on subsequent behaviors and thinking (e.g., Hershfield et al., 2011; Rutchick et al., 2018). The current intervention combines exposure to the future self with episodic future thinking, which refers to the capacity to imagine or to simulate experiences that might occur in one's personal future (Schacter et al., 2017). According to Suddendorf and Corballis (2007), humans have the capacity to ‘pre-live’ events by mentally projecting themselves forward in time, enabling them to plan for the future. This capacity has been used in interventions addressing lifestyle behaviors, such as food purchases (Hollis-Hansen et al., 2020), eating behaviors (Daniel et al., 2013), and smoking (Stein et al., 2016). The vividness of the imagined future event is an important factor in this process: The more vivid the prospective image is, the stronger the intervention effect (Daniel et al., 2013).

### Components of the smartphone-based intervention

1.2

Smartphone-based interventions have shown positive effects on a broad range of outcomes, such as depressive symptoms, anxiety symptoms, stress levels, and quality of life (Linardon et al., 2019). Research has started to link these effects to specific components used in applications. For instance, setting goals has been related to positive intervention effects in a randomized factorial trial examining the effectiveness of a smartphone application aimed at increasing physical activity (Fanning et al., 2017), as well as in a systematic review studying characteristics of efficacious smartphone-based interventions aimed at improving lifestyle choices (Schoeppe et al., 2016). Receiving personalized feedback on progress has also been associated with positive effects (Fanning et al., 2017; Schoeppe et al., 2016). Similarly, a meta-analysis examining components of smartphone-based interventions for mental health problems found that push notifications as reminders to use the application, and personalized feedback and supportive messages, were related to stronger intervention effects (Linardon et al., 2019).

### FutureU: a smartphone-based intervention

1.3

Building on earlier research, FutureU aims to stimulate a future-oriented mindset and personal goal attainment by strengthening people's ability and motivation to consider their future and fostering their identification with their future self. The intervention consists of three modules, each lasting seven days. The first module focuses on future self-identification and personality, the second on temporal distancing and wise reasoning in decision making, and the third on stimulating a growth mindset (Dweck and Yeager, 2019) and goal achievement. By engaging with their future self on a daily basis, we expect participants to gain a more vivid and positive view of their future and to incorporate their future self into their own identity. This positive vivid image of the future self and its integration into one's identity is expected to foster future-oriented mindset and behaviors (e.g., future orientation, reduced self-defeating behaviors, psychosocial well being), and personal goal attainment (Nurra and Oyserman, 2018; Verplanken et al., 2008).

The intervention includes components that have been related to positive intervention effects in prior interventions. Goal setting, personalized feedback, and supportive messages are implemented throughout the intervention. Participants set goals both at the start of the intervention and on a weekly basis during the intervention. Personalized feedback and supportive messages, which are partially based on participants' responses in the application, are communicated via the future self, such as the advice they formulate for their present self from the perspective of their future self. Although the feedback and support messages are not provided by a therapist, automatically generated personalized support has been shown to generate equivalent effects (Linardon et al., 2019).

We use technology to create a persuasive three-dimensional visual analog, an ‘avatar’, of participants' future self, and create the suggestion of interaction with this future self. Moreover, we developed an interaction within the application, a ‘time travel portal’, intended to facilitate mental time travel and alternating between taking the perspective of the future self and that of the present self. Furthermore, the intervention is standardized, ensuring intervention fidelity, and stimulates engagement with the application through the use of daily push notifications.

### The present study

1.4

The current study has three aims. First, we will examine users' experiences with the application and intervention adherence. This provides important information for the further development of the FutureU smartphone application, as high levels of acceptability and usability increases users' tendencies to apply the recommended intervention techniques (Sekhon et al., 2017). Second, we will analyze the overall effectiveness of the intervention. This will provide an indication about the extent to which the intervention is able to stimulate a future-oriented mindset, increase identification with the future self, promote beneficial behaviors, reduce self-defeating behavior, and foster personal goal attainment. Third, we will explore participants' change on several outcomes during the intervention to study the effectiveness of each module. We specifically focus on concepts in which changes can be measured over the course of a week, such as self-defeating behaviors (e.g., missing classes or work, overspending, procrastinating) and psychosocial wellbeing. Studying change on key outcomes after each module allows for determining which modules carry most promise for establishing change. This information provides detailed insights into how the intervention can be developed further to improve effectiveness and carries theoretical relevance (Fanning et al., 2017).

Given that interventions aimed at changing behavior are best implemented during a transformational life event and change of context (Dai et al., 2014; Verplanken et al., 2008), the target population of the current study is first-year university students. For many of these students transitioning from secondary school to university involves moving to a new city, living by themselves, being separated from family and close others, and/or taking on new roles. During transformational life events, people are more inclined to take a ‘big-picture’ view of their lives, which may motivate behavioral changes (Dai et al., 2014). Additionally, a change of context can alter choices and decisions based on contextual information in order to adapt to the new situation (Verplanken et al., 2008).

We hypothesize that participants experience the smartphone application as user friendly and engaging, and use it multiple times per week. Furthermore, we hypothesize that the intervention is effective in increasing students' future self-identification, future-oriented mindset and behaviors (e.g., increasing future-orientation, reducing self-defeating behavior), and personal goal attainment. Regarding the effectiveness of the separate intervention modules, we hypothesize to see positive intervention effects after each module, given that all modules are based on theoretical mechanisms of change. It is important to note, however, that to the best of our knowledge, this is the first time these theories of change are combined and incorporated in a smartphone application, which, in turn, may affect the effectiveness of these theorized mechanisms.

## Methods

2

### Design

2.1

The effectiveness of the intervention will be examined by means of a Randomized Controlled Trial (RCT) with two conditions: 1) a smartphone-based intervention condition, and 2) an active control condition. In the smartphone condition, participants receive the intervention over a period of three weeks. In the control condition, participants actively set goals, but will receive no further intervention.

All participants start with an individual intake session with a member of the research team in the lab at the university. During this session participants provide active informed consent, set goals for the coming month (i.e., monthly goal) and the year (i.e., yearly goal), and complete a series of questionnaires (baseline assessment). In addition, participants in the smartphone condition will take a photo of their face (a ‘selfie’) for avatar creation and install the application on their phone.

Assessments will be conducted prior, during, and immediately after the intervention, and at 3-month follow-up. Participants in the control condition will complete the assessments at parallel points in time. The outcomes will be assessed using online questionnaires (using Qualtrics software) completed by the participants. Academic results will be requested from the university at the end of the academic year after participants' consent. The interim assessments (one week and two weeks after baseline assessment) concern a subset of the outcomes. In exchange for participation, participants receive €25,- or 6 course credits after completion of the post-measurement, and an additional €10,- for completion of the 3-month follow-up (see Fig. 1 for the study flow chart).

**Fig. 1 f0005:**
[figure not shown]
Study flow chart.

Ethical approval for this study was obtained from the independent Ethics Board of the Institute of Education and Child Studies at Leiden University (ECPW2021-320).

### Participants and power calculation

2.2

Participants are first-year students enrolled in a university in the Netherlands who own an Android or iPhone smartphone. Sample size was determined by an a-priori power analysis with G*Power. Estimation of effect size is based on Tanner-Smith et al. (2018) who examined mean effect size distributions for universal interventions in a review of meta-analyses (Cohen's *d* ranging from 0.23–0.58). Assuming a significance level of *p* < .05, a medium effect size of Cohen's *d* = 0.50, two conditions, and one covariate, a sample size of 128 participants is estimated to achieve a power of 80%. Considering a drop-out rate of 20%, we aim to include 83 participants per condition, resulting in a total sample of 166 participants.

### Recruitment and randomization

2.3

Participants will be recruited via the university's official communication channels (e.g., university website, social media). Additionally, flyers will be distributed in university buildings. Furthermore, student associations will be requested to distribute the study advertisement among their members. Finally, the study will be advertised during the university's introduction week for incoming students, and announced at lectures for first-year students.

Interested students can schedule an appointment for the intake session. At the beginning of the session, students are screened for eligibility. Eligible students are randomly assigned to one of the two conditions on a 1:1 ratio, using block randomization with blocks of 6 (i.e., within a block 3 participants are allocated to each condition), and proceed with the intake session.

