### Blinding

2.4

It is not possible to blind participants or researchers to conditions as all will know whether they will be using the smartphone application or not. Participants are, however, unaware of the content of the application or the study's hypotheses.

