#### Intervention

2.5.1

During the intake, participants formulate a monthly- and a yearly goal. The goals can be related to each other, but this is not a requirement. Goal-setting is guided by the researcher to ensure that the goals are specific, measurable, and challenging but attainable, as goals with these characteristics are most likely to have a positive effect on performance (Van Lent and Souverijn, 2020). To this end, goals are determined using the SMART-goal model and Zimmerman's criteria (Ogbeiwi, 2021). Participants also formulate a weekly goal that will facilitate attainment of their monthly goal. During the intake participants independently formulate the first weekly goal, with a reminder of the researcher to consider the SMART-goal model. At the end of each week, participants indicate to which extent they have worked on, and reached, their goal of that week and independently formulate a new weekly goal.

Prior to this RCT, the first version of the FutureU application was extensively user-tested. Semi-structured interviews and focus groups were held among users belonging to the target population as well as experts (i.e., application developers, researchers, and a therapist with experience in smartphone-based interventions). User feedback was processed and used to further improve the application. An overview of module content and core features is provided in Table 1. For screenshots of the application, see Fig. 2.

**Table 1 t0005:** Modules of the intervention.

Week	Module	Aim	Theory	Core features
1	Future self and personality	Stimulating vividness, familiarity and identification with the future self and learn about their own and their future selves' personality	• Exposure to and vividness of the future self increases future orientation (McMichael et al., 2021). • Incremental personality theory: The belief that personality can change over time can reduce problematic behaviors (Yeager, 2017). • People's willingness to change on personality traits in socially desirable ways increases after feedback on their current trait levels (Thielmann and De Vries, 2021).	• Complete personal profile of the future self (e.g., work experience, skills, accomplishments) • Current scores on personality traits with an indication of norm scores • Psychoeducation that personality can change over time • Set scores of personality traits of future self

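### As written, allocation comes before goal setting and the T1 questionnaires in an unblinded trial, so the ANCOVA covariate and the coached yearly goal can be influenced by knowledge of the arm

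*Protocol article*

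**What the plan says.** The order of events has to be assembled from several sections of the protocol article.

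- **Section 2.3 (Recruitment and randomization).** "At the beginning of the session, students are screened for eligibility". Next: "Eligible students are randomly assigned to one of the two conditions on a 1:1 ratio, using block randomization with blocks of 6". Students then "and proceed with the intake session".
- **Section 2.1 (Design).** The content of that session is described as follows: "During this session participants provide active informed consent, set goals for the coming month (i.e., monthly goal) and the year (i.e., yearly goal"; participants also set to work on the T1 measures "and complete a series of questionnaires (baseline assessment". The smartphone arm additionally takes a selfie and installs the app.
- **Section 2.4 (Blinding).** "It is not possible to blind participants or researchers to conditions". Participants are, however, not told the app's content or the hypotheses.
- **Section 2.5.1 (Intervention).** For the monthly and yearly goals, "Goal-setting is guided by the researcher to ensure that the goals are specific, measurable, and challenging but attainable". Section 2.5.2 says the control arm follows the same procedure. Weekly goals are formulated by the participant alone in both arms.
- **Section 2.6.1 (Primary outcomes).** Goal commitment refers to the yearly goal.
- **Section 2.8 (Statistical analyses).** The arms are compared by ANCOVA with the baseline value of the outcome as covariate, and by latent growth curve models.

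**The concern.** ANCOVA on a baseline score gives an unbiased treatment effect because randomisation cannot have influenced the baseline. That guarantee is lost if the baseline is collected after participants learn their arm. The T1 measures are mostly self-reports on matters such as future orientation, self-defeating behaviour and identification with the future self. A student who has just heard that they will, or will not, use an app may answer differently. The adjustment then subtracts part of a difference that allocation itself produced.

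The goals raise a second issue. A researcher who knows the arm guides the yearly goal, and goal commitment, a primary outcome, is scored on that goal. Even without intent, the goals could come out differently in the two arms, and the commitment scores would then refer to different kinds of goal.

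**Working it through.** **Step 1. Order of events.** Placing section 2.3 next to section 2.1 gives: screening, allocation, remainder of the intake. The remainder includes goal setting and the T1 questionnaires. Section 2.4 makes the allocation open to both parties. The article nowhere states that the result is held back until T1 is finished.

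**Step 2. Scale of the planned effect.** Section 2.2 plans on d = 0.50, one covariate and a 5% level, and gives N = 128 for 80% power. An ANCOVA F test with f = 0.25, one numerator degree of freedom, two groups and one covariate gives power 0.801 at N = 128, so the figure reproduces (two-sided test assumed). This is 64 per arm.

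**Step 3. Bias formula.** In SD units, with baseline-post correlation r, the adjusted effect is

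(difference in post means) − r × (difference in T1 means).

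If allocation shifts T1 in one arm by s and leaves the post score unchanged, the bias is −r × s. Its direction depends on the direction of the shift: an intervention-arm T1 pushed up hides benefit, and one pushed down creates it.

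**Step 4. Illustration.** The documents give neither r nor s. The assumed ranges are r = 0.5 to 0.7 and s = 0.1 to 0.3 SD. The type I error is two-sided, by normal approximation, with SE = √((1 − r²) × 2/64).

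| r | s | size of bias, r × s | share of d = 0.50 | type I error (nominal 0.05) |
|---|---|---|---|---|
| 0.5 | 0.1 | 0.05 | 10% | 0.062 |
| 0.5 | 0.2 | 0.10 | 20% | 0.100 |
| 0.5 | 0.3 | 0.15 | 30% | 0.165 |
| 0.7 | 0.1 | 0.07 | 14% | 0.086 |
| 0.7 | 0.2 | 0.14 | 28% | 0.198 |
| 0.7 | 0.3 | 0.21 | 42% | 0.384 |

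If T1 is completed before allocation is known, s is zero in expectation and so is this bias.

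**Step 5. Which outcomes are reached.** Table 2 shows no T1 value for weekly goal achievement or academic results, so the covariate route cannot touch those two primary outcomes. Goal commitment is exposed twice: through its T1 score and through the coached yearly goal. The growth curve models also start from T1. A simple change from T1 to post would carry the whole shift s rather than r × s. The effect on a full growth model is not calculated here.

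**The case against.** The strongest reply is that being assigned is not the same as being told. Section 2.3 does not say when the result is disclosed. Section 2.1 lists consent, goals and questionnaires first and only then adds the selfie and installation, which is compatible with late disclosure. The flow chart (Fig. 1) is not available here and may settle the order. This limits confidence, but it does not answer the point. The only sequence stated in words puts allocation first, and if practice differs, section 2.3 needs rewording anyway.

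There are also real mitigations. Participants do not know the hypotheses or the app's content, the questionnaires are self-completed online so staff do not score them, and both arms follow the same goal-setting procedure. These make a large shift less likely. They do not mask the participant or the researcher.

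The illustration also assumes that the reaction to allocation touches T1 alone. If it persists into the post score, size and sign can differ.

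A reader might infer more than the article supports:

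- **Randomisation before consent, with losses that break intention-to-treat.** Section 2.1 places consent only somewhere within the session, so it may precede allocation.
- **Randomisation by unblinded staff.** The article does not say who generates, holds or reveals the sequence, and a condensed article may leave concealment to the full protocol.
- **Fixed blocks of 6 as part of the problem.** Block size cannot alter T1 or the goals. If staff tracked every earlier allocation in a block, 25% of allocations would be fully determined and the best guess right 68.3% of the time, but nothing shows that they do. Section 2.3 has students schedule their own sessions.
- **Coaching distorts attainment scores.** Attainment is scored on weekly goals that participants formulate independently. Only commitment is scored on a coached goal.

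**Conclusion.** The point holds for the sequence and no further. On the plain reading of sections 2.1, 2.3 and 2.4, goal setting and all T1 questionnaires follow an open allocation. The ANCOVA covariate in section 2.8 and the yearly goal behind the commitment score can therefore be influenced by knowledge of the arm. Confidence is moderate, because the moment of disclosure is not stated and the flow chart could not be seen.

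The range of 0.05 to 0.21 SD (10% to 42% of d = 0.50) shows what would be at stake. It is not an estimate: it rests wholly on the assumed shift, the assumed correlation and an unchanged post score. The point is still worth acting on, because a T1 score collected after disclosure cannot be restored later and prevention is almost free.

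**What to change.** Reword sections 2.1 and 2.3 so that the intake runs in this order:

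1. Screening.
2. Consent.
3. Monthly, yearly and first weekly goals.
4. All T1 questionnaires.
5. Allocation made or revealed.
6. Selfie and app installation, smartphone arm only.

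Only the last step differs between arms, so nothing in the article requires earlier allocation. The cost is a reordered session script, with no extra visit, staff or participants. The sample size stays as planned.

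If sessions have already run in the written order, report this and add a sensitivity comparison of post scores without T1 adjustment. A shift in T1 alone cannot bias that comparison. It does not repair goals that were themselves set with knowledge of the arm. It also costs precision: with 64 per arm the SE is √(2/64) = 0.177, against 0.153 with adjustment at r = 0.5 and 0.126 at r = 0.7.

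Randomly varied block sizes are at most an optional extra and are not needed to resolve this point.
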